## Abstract

**Background:**

In sub-Saharan Africa, malaria continues to cause over 10,000 maternal deaths and 75,000 to 200,000 infant deaths. Successful control of malaria in pregnancy could save lives of mothers and babies and is an essential part of antenatal care in endemic areas. The primary objective is to determine the protective efficacy of community-scheduled screening and treatment (CSST) using community health workers (CHW) against the primary outcome of prevalence of placental malaria. The secondary objectives are to determine the protective efficacy of CSST on maternal anaemia, maternal peripheral infection, low birth weight, selection of sulfadoxine-pyrimethamine (SP) resistance markers, and on antenatal clinic (ANC) attendance and coverage of intermittent preventive treatment during pregnancy (IPTp-SP).

**Methods/design:**

This is a multi-centre cluster-randomised controlled trial involving three countries with varying malaria endemicity; low (The Gambia) versus high transmission (Burkina Faso and Benin), and varying degrees of SP resistance (high in Benin and moderate in Gambia and Burkina Faso). CHW and their related catchment population who are randomised into the intervention arm will receive specific training on community-based case management of malaria in pregnancy. All women in both study arms will be enrolled at their first ANC visits in their second trimester where they will receive their first dose of IPTp-SP. Thereafter, CHW in the intervention arm will perform scheduled monthly screening and treatment in the womens homes. At time of delivery, a placental biopsy will be collected from all women to determine placental malaria. At each contact point, filter paper and blood slides will be collected for detection of malaria infection and SP resistance markers.

**Discussion:**

To reach successful global malaria control, there is an urgent need to access those at greatest risk of malaria infection. The project is designed to develop a low-cost intervention in pregnant women which will have an immediate impact on the malaria burden in resource-limited countries. This will be done by adding to the standard IPTp-SP delivered through the health facilities: an “extension” strategy to the communities in rural areas thus bringing health services closer to where women live.

**Trial registration:**

Current Controlled Trials: ISRCTN37259296 (5 July 2013), and clinicaltrials.gov: NCT01941264 (10 September 2013).

## Background

Malaria infection remains a major public health problem in (sub) tropical regions throughout the world. Approximately half of the world’s population is at risk of malaria and every year this leads to about 207 million clinical malaria cases [1].

In endemic countries, pregnant women have a higher risk of malaria compared to other adults due to the physiological hormonal changes and reduced immunity. In areas of stable, moderate to intense transmission, *Plasmodium falciparum* infection in pregnancy is often asymptomatic, yet it is an important contributor to maternal morbidity, preterm delivery, perinatal morbidity and mortality [2, 3] and may be associated with an increased risk of post-partum haemorrhage [4]. In areas of low, often unstable, transmission, malaria infection can evolve towards severe disease and result in maternal and foetal death. Such adverse outcomes are more frequent in primigravidae [5], in HIV-infected women [6] or in those from non-endemic countries as they do not have any immunity acquired before pregnancy [7]. The increased susceptibility of pregnant women to infection, and most specifically of primigravidae, is explained by the sequestration of *P. falciparum* in the placenta due to its affinity with the chondroitin sulphate A receptor. Placental malaria causes intrauterine growth retardation and the delivery of low birth weight babies who have a significantly higher risk of dying before their first birthday due to the reduced transfer of essential nutrients to the developing foetus as a result of the placental infection [7].

In sub-Saharan Africa, over 30 million women living in malaria endemic areas become pregnant each year [8], with malaria causing an estimated >10,000 maternal deaths and 75,000 to 200,000 infant deaths. In addition, it is responsible for 2 to 15% of maternal anaemia cases and up to 14% of low birth weight babies resulting in poor growth and development [9]. Furthermore, increasing evidence shows that placental malaria *per se* is associated with an increased risk of malaria infection and anaemia in the first and second year of life of the infant [10, 11], possibly mediated by the exposure to blood-stage malaria antigens *in utero* and the acquisition of a tolerant phenotype that persists into childhood [12]. Importantly, these effects are independent of low birth weight; that is, they can occur in any child born to mothers with placental malaria, and seem to be more pronounced in multigravidae [10]. If these observations are confirmed, the burden of malaria in African pregnant women would extend beyond that observed in primigravidae and could be vastly underestimated.

Successful control of malaria in pregnancy could save lives of mothers and babies and is an essential part of antenatal care in endemic areas [2, 3]. For sub-Saharan Africa, the World Health Organization has developed guidelines for the control of malaria in pregnancy consisting of a three-pronged approach:Prompt and effective management of uncomplicated malaria in the second and third trimester with artemisinin-based combination therapy. For the first trimester, it is recommended to combine quinine with clindamycin [13].Long-lasting insecticidal bed nets for all pregnant women in malaria-endemic countries [14].Intermittent preventive treatment during pregnancy with sulfadoxine-pyrimethamine (IPTp-SP) at regular intervals during pregnancy [15]. This is a simple, pragmatic policy that has proven very valuable in areas with stable, moderate to high malaria transmission. SP is safe when given in the second and third trimester of pregnancy, widely available, cheap and well tolerated. IPTp-SP can clear any existing malaria infection and provides post-treatment prophylaxis for a certain period of time, depending on SP sensitivity of local parasites [2].

Unfortunately, the coverage of long-lasting insecticidal bed nets and IPTp-SP in many sub-Saharan African countries remains low [14, 16], particularly in peripheral areas with difficult access to health facilities, leaving certain remote, poor populations out of reach of basic services. To add further complexities, SP resistance is increasing and, thus, there is the urgent need to develop alternatives or additional efforts to the current IPTp-SP policy [17].

### Study objectives

The project is designed to develop a low-cost intervention for pregnant women that will have an immediate impact on the malaria burden in resource-limited countries. In this study, it is proposed to add an “extension” strategy to the communities in rural areas in addition to the standard IPTp-SP delivered through health facilities. The novelty of this study is to bring health services closer to where women live, using community health workers (CHWs) to provide an antimalarial intervention to women with difficult access to the formal health system. The study will build on the use of CHWs who are already managing malaria cases within the framework of community case management of malaria (CCMm) [18].

The main aim is to establish whether maternal and infant health can be improved by adding to existing IPTp-SP at antenatal clinics (ANCs) community-scheduled screening and treatment (CSST) for malaria among pregnant women through CHWs. The study will test the primary hypothesis that CSST plus IPTp-SP will reduce placental malaria compared to IPTp-SP alone.

Primary objective: To determine the protective efficacy of CSST using CHWs against the primary outcome of prevalence of placental malaria.Secondary objectives: To determine the protective efficacy of CSST on maternal anaemia, maternal peripheral infection, low birth weight, selection of SP resistance markers, and on ANC attendance and coverage of intermittent preventive treatment during pregnancy.

These project objectives will be achieved through multidisciplinary research comprising clinical and bio-medical research, health system research, socio-economic and anthropological studies with a focus on CHW, involving policy makers right from the start of the project as full project partners (http://www.cosmicmalaria.eu).

## Methods/designs

### Study areas and participant eligibility

This is a multi-centre trial involving three countries with varying malaria endemicity: low (The Gambia) versus high transmission (Burkina Faso and Benin), and varying degrees of SP resistance (high in Benin [19] and moderate in Gambia and Burkina Faso [20]). This will ensure that the study outcomes would be broadly generalisable in order to facilitate the formulation of recommendations for both the West African region and other sub-Saharan countries. The Gambia, a country where malaria transmission has decreased to levels thought not possible a few years ago (and hence in a so-called “epidemiological transition”), will provide information possibly applicable to countries that may reach a similar status in the (near) future.

In The Gambia, the study is situated in the eastern part of the country on the southern bank of the Upper River Region (about 170,000 inhabitants). It will be centred around the Basse Health Centre and satellite health facilities. This is an area of seasonal malaria transmission (July-December) that has recently experienced a significant decline in malaria infections. Nevertheless, malaria remains a significant problem with about 15% of pregnant women with placental malaria at delivery as detected by histopathology [9].

In Burkina Faso, the study is situated in the centre-west of the country in the Nanoro health district catchment area (about 145,000 inhabitants). Malaria transmission is high and extremely seasonal and overlaps with the rainy season (June-October).

In Benin, the study is situated at the Atlantic Region in the southern part of the country, in the Glo-Djigbé, Zinvié and Zè district communities (about 136,000 inhabitants). Malaria transmission is perennial and the main burden of the disease occurs during the two rainy seasons (April-July and October-November).

The current treatment policy of uncomplicated malaria in pregnancy is oral quinine but artemisinin-based combination therapy (artemether-lumefantrine (AL)) may be used in the second and third trimester of pregnancy for all three countries, or amodiaquine-artesunate in Burkina Faso and Benin [21–23].

All pregnant women resident in the study area and willing to remain so until delivery will be invited to participate. Women who have a history of sensitivity to sulphonamides and vulnerable persons (for example, the mentally deficient) will be excluded. In The Gambia, pregnant adolescents younger than 16 years will not be enrolled unless consent is given by a responsible adult. In Burkina Faso and Benin, a pregnant woman is considered an adult if married (regardless of age). Study participants are free to withdraw from the study at any time without giving a reason.

Prior to the trial start, community sensitization and involvement of village leaders will be carried out at each study site. Appropriate community meetings will be held where the trial will be explained to all community members and consent at the community level to participate from community leaders will be obtained. Individual signed informed consent will also be obtained from all participants.

### Design

This is a multicenter, cluster-randomised controlled trial in which the CHWs and related catchment population (village/community) will be randomised to receive either the intervention (IPTp-SP plus CSST) or continue with current activities, that is IPTp-SP alone at health facilities during ANC visits (Figure 1).

**Figure 1 Fig1:**
[figure not shown]
**Schematic of study design.** ANC, antenatal clinic; CHW, community health worker; CSST, community-scheduled screening and treatment; FA, field assistant; IPTp-SP, intermittent preventive treatment during pregnancy with sulfadoxine-pyrimethamine; RDT, rapid diagnostic test.

### Study procedures

#### All communities

In principle, the first point of contact with pregnant women is at the first ANC visit. Here, the study will be explained to the woman and informed consent will be obtained. If the woman is in the early stage of pregnancy, she will be encouraged to return during her second trimester for IPTp-SP. If the woman is in the second or third trimester stage, health staff will give the first IPTp-SP dose and plan the second one onto the ANC card at least 1 month after the first dose. A data collection form on health and socio-demographic factors and a physical examination will be carried out, and a blood slide and a blood sample on filter paper will be collected for detection of malaria infection and SP resistance markers (Figures 1 and 2). All women will be encouraged to deliver at the health facility. If women do not attend the ANC, consent will be obtained at village level.

**Figure 2 Fig2:**
[figure not shown]
**Schedule of events.** Symbols are from thenounproject.com collection: ‘baby’ symbol (1), ‘baby’ symbol (2) by Edward Boatman, ‘house’ symbol by Marco Olgio, ‘medicine’ symbol by Emmanual Mangatia, ‘medicine’ symbol by Paulo Volkova, ‘doctor’ symbol by Paulo Volkova, ‘pointer’ symbol by Evan MacDonald and ‘drop’ symbol by Eric Bergholz. ANC, antenatal clinic; Hb, haemoglobin; IPTp; intermittent preventive treatment during pregnancy.

#### Intervention communities

CHWs allocated to the intervention arm will follow specific training on community-based case management of malaria, the need for monthly testing of pregnant women using a rapid diagnostic test (RDT), and on issues related to malaria in pregnancy, including the benefit of IPTp-SP and administering SP as early as possible in the second trimester of pregnancy.

The CHWs will continuously identify all pregnant women in their own catchment area, visit eligible women in their home and encourage them to attend the ANC as early as possible in their pregnancy for enrolment. The CHW will check after a week if the ANC was visited. For women who do not attend the ANC, the CHW will further encourage and discuss reasons for non-attendance.Thereafter, at monthly intervals up to the last week of gestation, the CHW will revisit the study participant’s house (Figure 2). The CHW will collect a blood slide and a blood spot on filter paper, perform a RDT and administer a full course of AL to any woman with a positive RDT. In case of treatment, the CHWs will return to assess uptake and compliance by administering a short questionnaire and checking the empty packaging of the treatment at the end of the course.

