#### Control communities

In control communities, CHW will not be trained to administer RDT and AL to pregnant women. The women will be mainly followed through their attendance to the health facilities at the ANC.

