### Analytical plan

Appropriate summary statistics (that is, mean and standard deviation for normally distributed variables and median and inter-quartile range for non-normally distributed variables) will be used to describe the baseline data.

The primary analysis will compare the prevalence of placental malaria (defined as number of positive samples by total number of samples) between the intervention and the control group.

Secondary analysis will compare the following variables between trial arms: (i) mean haemoglobin levels and prevalence of anaemia (haemoglobin <11 g/dL) at delivery, (ii) prevalence of *P. falciparum* peripheral infection (microscopy and PCR) at delivery and during pregnancy, (iii) mean birth weight and proportion of newborns with low birth weight (<2,500 g) between the two trial arms, (iv) level of ANC attendance by village/cluster and coverage of IPTp-SP (defined by number of doses completed during pregnancy), and (v) SP resistance markers profiles.

For the primary and secondary analysis both linear regression (for continuous outcomes such as haemoglobin levels) and logistic regression (for binary outcomes such as placental malaria) will be used to quantify the difference between trial arms. The regression models will allow for the multi-level structure of the data (that is, individuals within villages) using random effects and for all relevant co-variates to be taken into account. Model assumptions will be checked to confirm reliable estimates.

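### Active identification of pregnant women after randomisation is described for intervention villages only, and ANC attendance and IPTp-SP coverage have no denominator common to both arms

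*Protocol article*

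**What the plan says.** The Design section describes a "cluster-randomised controlled trial in which the CHWs and related catchment population (village/community) will be randomised". Individual women are therefore identified and enrolled after their village has been allocated.

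For intervention villages (Intervention communities), "The CHWs will continuously identify all pregnant women in their own catchment area, visit eligible women in their home". The purpose of this contact is early ANC attendance, since the ANC is where enrolment happens. The CHW checks a week later, and "For women who do not attend the ANC, the CHW will further encourage and discuss reasons for non-attendance".

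For control villages (Control communities), the text says that CHWs are not trained to give RDTs and AL to pregnant women, and that "The women will be mainly followed through their attendance to the health facilities at the ANC".

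On enrolment, the Abstract states that "All women in both study arms will be enrolled at their first ANC visits in their second trimester". The section All communities also places consent at the first ANC visit, with the first SP dose given there if the woman is in her second or third trimester, and adds: "If women do not attend the ANC, consent will be obtained at village level". The Sample size rationale speaks of each CHW recruiting women, without separating the arms.

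On outcomes, Secondary endpoints lists IPTp-SP coverage by village or cluster, number of ANC visits and number of SP doses. The Analytical plan compares ANC attendance by village or cluster and "coverage of IPTp-SP (defined by number of doses completed during pregnancy". Neither section gives a denominator. The only register described (Data handling and record keeping) is held at each clinic.

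**The concern.** The Discussion states that CHW encouragement is meant to raise IPTp-SP coverage. The women who would otherwise stay away are thus the group in which a coverage effect should appear. In intervention villages a trained person looks for them and sends them to be enrolled; for control villages no such route is described beyond the village-consent sentence.

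Enrolment is also tied to the outcome. A woman enrolled at the ANC has, by definition, made at least one visit, and in her second or third trimester she gets a first SP dose there. Attendance or coverage figures taken from enrolled women are then conditioned on what the intervention is meant to change. The control denominator would lean towards spontaneous attenders, while the intervention denominator would also hold women who are harder to reach and may complete fewer doses.

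At stake is a stated secondary objective, the effect on ANC attendance and IPTp-SP coverage. The primary comparison is exposed by the same route: the Discussion links low coverage to distance, poverty, education and age, so women brought in mainly in one arm may have a different risk of placental malaria.

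**Working it through.** **The plan's recruitment figures.** From the Sample size rationale: 800 people × 5% = 40 women per year; 40 × 1.5 years = 60 per cluster; 60 × 30 clusters = 1,800 per country; × 3 = 5,400. These reproduce. The plan states no figure for attendance or coverage.

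The Randomisation section selects villages of about 1,000 to 2,000 people. The same 5% over 18 months gives 1,000 × 0.05 × 1.5 = 75 to 2,000 × 0.05 × 1.5 = 150 expected pregnancies. The minimum of 60 is then 60/75 = 80% down to 60/150 = 40% of them. Reaching 60 in every cluster would not show that both arms captured the same share of pregnancies.

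**Illustration (all inputs assumed).** Take 100 pregnancies per village.
- Control: 60 attend unprompted and enrol, and 40 of these take two or more doses. The other 40 women take none and are not enrolled.
- Intervention: the same 60 women with the same 40 covered, plus 30 brought in by the CHW, of whom 9 are covered.
- Among enrolled women: 40/60 = 67% versus (40 + 9)/90 = 54%, an apparent harm.
- Among all pregnancies: 40/100 = 40% versus 49/100 = 49%, a benefit.

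**Break-even.** Let x control non-attenders be enrolled through village consent, with no doses. The enrolled-only figures are equal when 40/(60 + x) = 49/90, so x = 40 × 90/49 − 60 = 13.5. At x = 14: 40/74 = 54.1% versus 54.4%, no reversal. At x = 30: 40/90 = 44% versus 54%, a benefit.

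**Sensitivity to the assumptions.** Let A be the share attending unprompted with coverage cA, and N = 1 − A the rest. A share r of N is enrolled, with coverage cN in the intervention arm and 0 in control. Coverage among enrolled women is (A·cA + N·r·cN)/(A + N·r). Village coverage is A·cA + N·r·cN. In the table r is 80% in the intervention arm, and cA and cN are in percent.

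| A | cA control / interv. | cN | r in control | Village effect (points) | Effect among enrolled (points) |
|---|---|---|---|---|---|
| 60% | 70 / 70 | 30 | 0% | 42.0 vs 51.6 (+9.6) | 70.0 vs 56.1 (−13.9) |
| 80% | 60 / 60 | 30 | 0% | 48.0 vs 52.8 (+4.8) | 60.0 vs 55.0 (−5.0) |
| 90% | 60 / 60 | 30 | 0% | 54.0 vs 56.4 (+2.4) | 60.0 vs 57.6 (−2.4) |
| 60% | 70 / 70 | 30 | 30% | +9.6 | 58.3 vs 56.1 (−2.2) |
| 60% | 70 / 70 | 30 | 80% | +9.6 | 45.7 vs 56.1 (+10.4) |
| 80% | 60 / 70 | 40 | 0% | 48.0 vs 62.4 (+14.4) | 60.0 vs 65.0 (+5.0) |

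If attenders' coverage is unchanged and no control non-attenders are enrolled, the sign reverses whenever the newly reached women have lower coverage than the spontaneous attenders. If control non-attenders are enrolled as fully as intervention ones, the reversal goes. If attenders' own coverage also rises, the effect is diluted rather than reversed.

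**The case against.** Four points can be made for the plan.

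1. CHWs refer women; enrolment itself is at the ANC in both arms. That stands. The asymmetry lies in who looks for women and pursues them, not in who signs them in.

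2. A reader might infer that nobody looks for non-attenders in control villages. The documents do not say so. The village-consent sentence stands under All communities, and the control text says only that follow-up is mainly through the ANC. The legend of Figure 1 also lists a field assistant, a role the text never describes, and the figure itself was not available for this check. What remains is that the text names nobody to find control non-attenders, while it describes the search in intervention villages in detail.

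3. A reader might also infer that coverage is fixed as doses per enrolled woman. That is not stated. Coverage by village or cluster is listed separately from number of doses, and a condensed article may leave a denominator to a fuller document. The missing denominator alone would not be a finding. It matters because the identification procedure that is stated differs by arm, and because ANC enrolment and a clinic-held register point towards an enrolled-women denominator.

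4. Reversal needs low enrolment of control non-attenders and little gain among women who would have attended anyway. This stands: reversal is possible, not shown to be likely.

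For the primary outcome, the Analytical plan already allows for covariates. That helps, but it does not say which covariates are safe to use when one arm's CHWs influence the timing of enrolment.

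**Conclusion.** The concern holds in a limited form. After randomisation, active identification and pursuit of pregnant women is described for intervention villages only, and attendance and coverage have no denominator that is the same in both arms. If they are computed among enrolled women, the effect may be diluted or, when few control non-attenders are enrolled, reversed. On the assumed figures 40% versus 49% becomes 67% versus 54%, and the reversal ends at about 14 of 40 control non-attenders enrolled. The documents give none of the attendance or coverage inputs, so these figures show a mechanism and do not predict a result.

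For placental malaria the enrolled groups may differ in risk. The documents do not allow the size to be estimated, and it would be wrong to conclude that the primary comparison is invalid. The point should be settled while recruitment is ongoing, as the Trial status section says it is.

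**What to change.** - **One denominator rule.** Analyse ANC attendance and IPTp-SP coverage at cluster level in both arms. Denominator: expected pregnancies = village population (already obtained for randomisation) × 5% × recruitment time. Numerator: the clinic register of all pregnant women, tabulated by village. First confirm that the register records village and SP doses.
- **Show the capture.** Report enrolled/expected pregnancies by arm.
- **Primary analysis.** Adjust for gravidity and age, which CHWs cannot alter. Do not adjust for gestational age at enrolment, which CHWs are asked to bring forward.
- **Reconcile the text.** The Abstract, All communities, Intervention communities, Control communities and Sample size rationale should give one account of who identifies and recruits women in each arm, and where.

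A sensitivity analysis excluding women consented at village level is tempting but should not be used. It conditions on ANC attendance, which CHWs change, and leaves CHW-persuaded attenders in the intervention arm.

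**Cost.** Analysis wording and tabulation of registers by village, with no new visits if the register holds the needed fields. The 5% figure is approximate and adds noise between villages, but the rule is the same in both arms.
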